## Abstract

**Background:**

In Burkina Faso, nearly half of the population is under 15 years old, and one in four adolescents experience depression. This underscores the critical need to enhance mental health literacy among adolescents and youth, empowering them to manage their mental well-being effectively. Comic books offer an engaging approach to health education, yet their effectiveness in addressing mental health remains largely untested. Our study aims to fill this gap by evaluating the effectiveness of comic books in enhancing mental health literacy among adolescents and young adults aged 10–24 years.

**Methods:**

We will recruit 2,007 participants aged 10–24, stratify them by age, and randomly assign them to three groups (1:1:1): a comic book intervention group (Intervention 1), a text-only flyer group (Intervention 2), and a control group with no intervention. The primary outcome will be mental health literacy and secondary outcomes will include anxiety, depression, and intentions to cope.

**Discussion:**

We hypothesize that the comic book intervention and flyer intervention will prove more effective in improving mental health literacy than the control group. We further hypothesize that for younger adolescents (10–14), the comic book will be more effective at increasing mental health literacy than the flyer. Conversely, we hypothesize that the flyer will be more effective in increasing mental health literacy for older adolescents (15–24). Our study will provide evidence on novel interventions designed to enhance mental health literacy among adolescents and young adults in low-resource settings.

**Trial registration:**

This trial has been registered on the German Clinical Trials Register (DRKS), with the registration number DRKS00034242.

**Supplementary Information:**

The online version contains supplementary material available at 10.1186/s12889-025-21325-2.

## Introduction

It is estimated that one in seven adolescents experiences a mental disorder globally, yet this vulnerable group is largely undiagnosed and untreated [1]. The World Health Organization categorizes adolescents from the ages of 10 to 19 years of age and youth as 15 to 24 [2]. This mental health crisis for adolescents and youth is especially critical in low-and middle-income countries (LMICs), where the high demand for quality mental health services is often met by low supply, as seen in Sub-Saharan Africa (SSA) [3, 4]. Burkina Faso, one of seven SSA countries ranked in the lower 5th percentile out of the Human Development Index [5], exemplifies this issue. While Burkina Faso has over 20 million inhabitants, there are only eleven psychiatrists, eighty-six nurses specialized in mental health, five psychologists, and ten neurologists who are practicing in the public healthcare systems [6].

A national survey from 2015 indicated that 41.5% of Burkina Faso’s population currently suffers from at least one mental disorder, with depression being the most common [7]. The country also has a very young population, with almost half (45.3%) under 15 years old [6]. Approximately one in four adolescents aged 10 to 19 years (26.4%) in Burkina Faso reported experiencing depressive symptoms [8]. Another study surveyed Burkina Faso youth aged 12 to 20 years on the prevalence of self-injurious thoughts and behaviors and found that 8% of 12–13-year-olds reported life was not worth living, with this percentage increasing to 20% among 18–20-year-olds [9].

Burkina Faso’s 2020–2024 Mental Health Strategic Plan [6] identifies several priority areas, including conducting mental health research (Priority Area 6) and focusing on specific groups such as adolescents (Priority Area 13). Advancing research on adolescent mental health can focus on promotion, prevention, and/or treatment. The WHO recommends increasing mental health knowledge and understanding as a strategy to prevent and promote mental health issues [10]. Increasing mental health literacy (MHL) in this population represents an essential intervention pathway to understand mental health conditions, their symptoms, causes, and available treatments.

The concept of MHL is defined as “understanding how to obtain and maintain positive mental health; understanding mental disorders and their treatments; decreasing stigma related to mental disorders, and enhancing help-seeking efficacy” [11, 12]. Individuals with high MHL are better equipped to make informed decisions about mental health treatment and use effective coping strategies [13]. While adolescents and youth broadly have lower rates of MHL [14], this problem is more pronounced in LMICs [15]. Most of the studies that target MHL take place in high-income countries and depend on the availability of trained mental health professionals, such as therapists, psychiatrists, and social workers, to deliver the interventions [16]. This furthers the need for MHL interventions delivered by non-specialist health providers (NSHPs) such as teachers, lay health workers, and community health workers [17].

In resource-constrained settings it can also be important to intervene efficiently. “Light-touch” interventions are low-cost and minimally invasive interventions [18]. Light-touch interventions are typically aimed at improving psychological well-being for the subclinical population [19]. Such interventions have been demonstrated to improve mental health in low-income settings [20].

Many government organizations create brochures to educate the public on the basics of mental health education (see https://www.nimh.nih.gov/health/publications). The use of brochures to increase health literacy is a widespread practice, and there have been mixed results regarding whether a brochure is more effective than a more visually engaging delivery mechanism, such as an illustrated brochure, brochure with photographs, or video [21].

Comic books offer a low-cost, engaging approach to health education, accessible to varying literacy levels by providing pictures that provide visual explanations of the text [22]. A comic's “fun factor” of a comic draws in individuals who would otherwise be reluctant to read text-only narratives [23]. There is some evidence that comic books are especially effective for an adolescent population in communicating health knowledge [24]. However, to the best of our knowledge, there have been no randomized control trials testing the effectiveness of using a comic book to improve MHL for adolescents and youth in LMICs.

This study aims to evaluate whether an illustrated comic book or a brochure-like flyer (text-only) that describes the mental disorders of anxiety and depression as well as information around help-seeking and coping, is more effective at increasing mental health literacy for certain age groups. We hypothesize that both the comic book and the flyer will increase mental health literacy for all ages compared to a control group that receives no intervention. However, we hypothesize that the comic book will be more effective in increasing mental health literacy with younger adolescents (ages 10–14) compared to older adolescents and youth (ages 15–24) due to the engaging nature of illustrations for young readers. The primary outcome will be mental health literacy and secondary outcomes will include anxiety, depression, and intentions to cope. We will also explore how the information in the comic book and flyer might impact anxiety and depression scores as previous studies have shown that at times, individuals are negatively impacted after consuming information about depression [25]. The primary and secondary outcomes will be assessed directly following the implementation of the intervention for the comic book and flyer groups.

## Methods

### Participants and recruitment

This randomized controlled trial study is part of the research grant DASH for the design and evaluation of adolescent health interventions and policies in Sub-Saharan Africa (SSA). DASH is a network comprising public health research and training institutions from seven SSA countries (Burkina Faso, Ethiopia, Ghana, Nigeria, South Africa, Tanzania, Uganda), as well as Germany and the United States. It aims to address critical research gaps related to the need for interventions and policies and their design, evaluation, and transportability across three domains: nutrition and physical activity, sexual and reproductive health, and mental health and violence (https://dash-rhissa.org/). This trial is integrated into the initial round of longitudinal data collection of a cohort of adolescents and young adults for each country, which will hereafter be referred to as the ‘DASH cohort study’. A Health and Demographic Surveillance System (HDSS) operates in each of the study communities, meaning that the DASH cohort study can use existing sampling frames of the full population to sample and recruit participants.

Within the DASH cohort study, we will sample and recruit 2,007 adolescents and youth aged between 10 and 24 years (with equivalent proportions from the age categories 10–14; 15–19; and 20–24 years) in the Burkina Faso study community. Where the initial sample is not sufficient to reach 2,007 participants due to refusal to participate or incorrect sampling frames, we will draw further individuals from the existing sampling frame, until 2,007 participants are enrolled. These individuals will be followed up annually for four waves of data collection. This sample of 2,007 will also serve as the study sample for this trial.

## Sample size and power considerations

To estimate the sample size and conduct the power analysis, we used the *R* package “Pwr” and the statistical software *G*Power* [26]. We calculated the minimum detectable effect size (MDE) for primary and secondary outcomes, which represents the smallest effect size that would be sufficient to detect statistical significance, based on a predetermined level of significance (*α*), sample size (*N*), and statistical power (1—*β*). We began by computing the power for t-tests of means to achieve a target power of 0.80. This process was conducted separately for each of the two waves in our study, which include three treatment arms and three age subgroups. In our calculations, we used the guideline* α* = 1 − (1 − 0.05) ^(1/√*h*) [27], where *h* was computed based on the number of treatment arms and outcomes. The overall sample size was set at *N* = 2007. For Wave 1, we allocated the sample size as N/3 per treatment arm. Anticipating a 10% attrition rate for follow-up measurements in Wave 2, the adjusted sample size was calculated as *N* = *n* = (sample/3) * (1—attrition). For the subgroup analysis in Wave 1, the sample size per age subgroup was assumed as *N* = sample/9, (i.e., N divided by 3 treatments arms * 3 age subgroups). Similarly, the adjusted sample size for Wave 2 subgroup analysis, the adjusted sample size was *n* = (sample/9) * (1—attrition). We used *R* Power to input the calculated MDEs and illustrate how each subgroup sample size corresponds to power levels (See Table 1).

**Table 1 Tab1:** Required sample size and minimum detectable effect size (MDE) for each wave and full and subgroups

Sample	Treatment (N)	Comparison (N)	Cohen’s *d* Wave 1	Cohen’s *d* Wave 2
Full treatment (Comic book, Flyer, Control)	669	669	0.17	0.18
Age sub-groups	223	223	0.32	0.34

There is a lack of studies investigating the impact of comic book intervention on mental health literacy in Africa. To ensure that the calculated effect estimate is something that we could reasonably expect, we compare our calculated effect sizes with those from a related study in a non-mental health domain. Shin and colleagues (2022) investigated the effectiveness of a comic book intervention in East Africa on knowledge about human papillomavirus (HPV) types [28]. They reported that the mean percentage of correctly answered questions about HPV pre-intervention was 44%, which increased to 82.9% post-intervention. The study included a sample size of *n* = 64 for the pre-test and *n* = 72 for the post-test assessments. Cohen's d effect size was calculated using the following formulas.$$d=\frac{Mean1-Mean2}{PooledStandardDeviation}$$$$PooledSD=\sqrt{\frac{\left(n1-1\right)*{SD}^{2}1+\left(n2-1\right)*{SD}^{2}2}{n1+n2-2}}$$

This resulted in Cohen’s *d* = 3.58, which indicates a large effect size.

In addition, there was a previous study on age differences in mental health literacy [19] that used Cohen’s *h* values, a measure similar to Cohen’s *d* but applicable to differences between proportions or probabilities. A difference with *h* = 0.2 is considered “small”, *h* = 0.5 indicates a “medium” difference, and *h* = 0.8 represents a “large” difference. Their findings revealed that adults aged 70 years exhibited lower accuracy in identifying depression symptoms compared to those aged 18–24 years (Cohen’s *h* = 0.64), 25–39 years (*h* = 0.61), 40–54 years (*h* = 0.53), and 55–69 years (*h* = 0.50). Based on this, we assume a medium effect size for the impact of age on mental health literacy. In summary, our sample size is likely adequate for detecting both large and medium effect sizes, as observed in previous studies.

## Procedure

In this randomized controlled trial, each participant will be randomly assigned (1:1:1) to receive either a comic book (Intervention 1, 15 min long) a flyer (Intervention 2, 15 min long), or no intervention (Control). The randomization process will be stratified for the age category (i.e., 10–14 years; 15–19; 20–24) to ensure that within each category, a similar number is allocated to each arm (see Fig. 1). The allocation sequence will be generated by colleagues at the Technical University of Munich, who are not further involved in the conduct of the trial. They will use statistical computing software to define a random allocation sequence for all potentially eligible participants included in the pre-defined sample roster.

**Fig. 1 Fig1:**
[figure not shown]
Trial flow chart

As part of the DASH cohort study, which this trial is nested, all participants will take part in a survey interview of approximately 60–90 min. Each interview will begin with the data collector providing the consent form. If the participant consents, they will be asked survey questions regarding mental health literacy, anxiety, and depression before the intervention is administered, which will serve as baseline measures. For participants assigned to the comic book intervention, the data collector will provide the printed comic book to the participants, reading the text aloud. For participants assigned to the flyer intervention, the process will be the same where the data collector will provide the printed flyer, reading the text out loud. Participants in the control group will be provided with no additional instructions or interventions. Participants will then be asked other survey questions regarding sexual and reproductive health providing a brief break between the intervention implementation and the post-intervention survey. All participants will be surveyed on mental health literacy, anxiety, depression, and intentions to cope as a post measure.

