## Outcome measures

Our primary outcome will be the sum score on a revised version of a Universal Mental Health Literacy Scale for Adolescents (UMHL-A) [30], measured both before and after the intervention in wave 1 and a year later in wave 2. This scale assesses mental health literacy across domains such as mental health knowledge, mental disorder knowledge, help-seeking behavior, and stigma. The revised UMHL-A consists of 10 items, each rated on a 5-point Likert scale (1–5 points), yielding a total score ranging from of 10 to 50. Higher scores indicate a greater level of mental health literacy. Our secondary outcomes will include the total scores on the 2-item Patient Health Questionnaire (PHQ-2) [31, 32], the 2-item Generalized Anxiety Disorder (GAD-2) [32, 33], and the 2-item Intentions to Cope scale [34], all measured post-intervention.

Outcome assessment will happen as part of waves 1 and 2 of the DASH cohort study; as part of the DASH cohort study, an attempt will be made to identify and follow-up all participants from wave 1 in wave 2. Outcomes will be assessed during the survey interview conducted by a data collector. All data collectors will be trained in administering the full survey, which should ensure outcomes are collected for all participants. All scales used in our study will be translated into French and reviewed by local mental health experts for cultural sensitivity. To assess reliability, we will calculate Cronbach’s alpha within our sample [35].

First level of data entry and storage will be on a tablet before forms can be uploaded online. At this level only data collectors involved in the interview and/or data manager will have access to the data collected. Data collectors are responsible for privacy and confidentiality of the data on the device. Second level of data storage will be on the online server. Application developers will be responsible for setting up the server for online data storage. Server setup will include password protected access and different levels of access to ensure only authorized individuals can access the data online and only access their allowable sections of the application and/or data sources.

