## Data analysis

We will assess participants’ sociodemographic characteristics, including age, gender, education levels, ethnicity, religion, household characteristics, and their parents’ highest level of education and occupation with outcome measures. To assess the effectiveness of an intervention on mental health literacy (MHL), we will build a multiple regression model. We will also assess each sub-scale component of MHL (knowledge about mental health, knowledge about mental health, help-seeking, and stigma). Here, the independent variable is “3 arms”, representing different intervention groups, and the outcome will be “MHL after the intervention.” We will control for baseline MHL scores by including them as a covariate, following the recommendation by Senn (2006) to adjust for potential baseline differences [36]. For the analysis, we will employ dummy coding for the three trial arms to compare each intervention arm against the control arm. In addition, covariates such as depressive and anxiety symptoms, intentions to cope, age, gender, and education levels will be included in the model. Secondary outcomes will be examined using three separate linear regression models, with the trial arm” treated as a factor and the control arm serving as the reference category for each secondary outcome. To ensure the validity of our multiple regression analysis, we will calculate variance inflation factor values to check for multicollinearity among the independent variables. We will conduct statistical analyses using *R version 4.1.0* (www.r-project.org).

The final cleaned, de-identified and locked dataset of the trial will be accessible by the DASH network partners. Public access to the data will be made available upon review of the request and approval by each institute’s Principal Investigators.

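### Intentions to Cope is the only outcome with no described pre-intervention measurement, so its comparison cannot be adjusted for its own baseline: a minor efficiency loss on a secondary endpoint

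*Protocol article*

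**What the plan says.** The Procedure section of the protocol article sets out the wave 1 interview. Before the material is given, "they will be asked survey questions regarding mental health literacy, anxiety, and depression before the intervention is administered, which will serve as baseline measures". After the material and a short block on another topic, "All participants will be surveyed on mental health literacy, anxiety, depression, and intentions to cope as a post measure". The second list is the first plus Intentions to Cope.

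Outcome measures states that the primary outcome, mental health literacy (MHL), is "measured both before and after the intervention in wave 1 and a year later in wave 2". It then lists the three secondary outcomes, PHQ-2, GAD-2 "and the 2-item Intentions to Cope scale [34], all measured post-intervention".

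For the primary outcome, Data analysis says: "We will control for baseline MHL scores by including them as a covariate". It also says that "covariates such as depressive and anxiety symptoms, intentions to cope, age, gender, and education levels will be included in the model". For the others: "Secondary outcomes will be examined using three separate linear regression models", with trial arm as a factor and control as reference. No baseline covariate is named there for any secondary outcome.

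**The concern.** A score taken before the intervention usually predicts the score taken after it, and adjusting for it narrows the confidence interval of the arm contrast. The schedule allows this for MHL, PHQ-2 and GAD-2. For Intentions to Cope it does not, and no reason is given. Analysis choices for the other outcomes can still be settled in an analysis plan. This one cannot, because once a participant has seen the comic book or flyer the pre-intervention value is gone.

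At stake is the precision of one secondary comparison, and the ability to describe the arms on prior coping intentions. The covariate list for the MHL model is also affected: it includes intentions to cope, but the only wave 1 measurement that the article describes comes after the intervention.

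**Working it through.** **Which outcomes have a pre-intervention value (Procedure; Outcome measures)**

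| Outcome | Before | After |
|---|---|---|
| MHL (primary) | yes | yes |
| Anxiety (GAD-2) | yes | yes |
| Depression (PHQ-2) | yes | yes |
| Intentions to Cope | not described | yes |

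The statement in Outcome measures that the secondary scales are taken post-intervention does not settle the matter alone: it also covers PHQ-2 and GAD-2, whose constructs are in the pre-intervention list. The evidence is the pair of lists in Procedure.

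**Reproducing the plan's figure.** Inputs from the sample size section: 669 per arm, "computing the power for t-tests of means to achieve a target power of 0.80", and α = 1 − 0.95^(1/√h). The value of h is not printed, so I varied it; two-sided testing is assumed. The minimum detectable effect is (z(1−α/2) + z(0.80)) × √(2/n).

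- h = 4: α = 0.0253, giving 0.168.
- h = 6: α = 0.0207, giving 0.173.
- Plain α = 0.05 gives 0.153, which does not match.

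Both h = 4 and h = 6 round to the stated 0.17. That figure therefore corresponds to a comparison without covariate adjustment, and the section says that the detectable effects apply to secondary as well as primary outcomes.

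**Effect of own-baseline adjustment.** With pre–post correlation r, the residual variance is (1 − r²) times the outcome variance. The detectable effect becomes 0.17 × √(1 − r²), and the equivalent unadjusted sample size per arm is 669 / (1 − r²). The documents do not give r, so a range is assumed. Power is at d = 0.17 with h = 4, where it is 0.81 unadjusted.

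| r (assumed) | Variance cut (r²) | Detectable effect | Equivalent n per arm | Power |
|---|---|---|---|---|
| 0.2 | 4% | 0.167 | 697 | 0.83 |
| 0.3 | 9% | 0.162 | 735 | 0.85 |
| 0.5 | 25% | 0.147 | 892 | 0.91 |
| 0.6 | 36% | 0.136 | 1,045 | 0.95 |

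**If other covariates are already in the model.** The table compares own-baseline adjustment with no adjustment. Suppose other baseline covariates explain 10% of the variance, and together with the own baseline they explain 25%. The extra reduction is then 1 − 0.75/0.90 = 17%, not 25%.

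**The case against.** The strongest reply is that nothing here is an error. A post-only comparison of randomised arms is valid, and with 669 per arm any chance imbalance in prior coping intentions is small on average and already reflected in the standard error. A 2-item scale may have a low pre–post correlation, in which case the gain is 4–9%. Asking the same intention items twice in one sitting may also lead participants to repeat their first answer or may prime them, and equal administration across arms does not fully remove that. All of this stands, and it limits the point to efficiency. It does not remove the point, because the plan already accepts repeat asking for the other three outcomes.

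A reader might infer more than the documents support:

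- *That the endpoint cannot be baseline-adjusted at all.* Only its own baseline is missing. Baseline MHL, PHQ-2 and GAD-2 scores, age, gender and education can still be used.
- *That the schedule breaks a plan-wide rule of baseline adjustment.* The own-baseline sentence concerns MHL only. As described, Intentions to Cope would be modelled like the other two secondary outcomes, so new items bring no precision unless its model also uses them.
- *That the loss falls on the secondary outcome most able to move within one interview.* The article does not say so. Its Introduction says that the trial will explore effects of the material on anxiety and depression scores.
- *That the MHL model certainly adjusts for a post-intervention value.* Data analysis gives no timing for that covariate. The list may presuppose a baseline measurement that Procedure does not describe.

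**Conclusion.** The point holds as a minor efficiency loss on one secondary endpoint. On the schedule described, the Intentions to Cope contrast cannot use its own baseline, and the randomised comparison stays unbiased. The size rests wholly on an assumed correlation: over r = 0.2 to 0.6, the forgone variance reduction runs from about 4% to 36% against an unadjusted analysis, and is smaller if other baseline covariates already explain part of the variance. Even at r = 0.5 the detectable effect moves only from 0.17 to about 0.15. This is a cheap improvement rather than a correction, but it has to be made before participants are interviewed.

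**What to change.** In Procedure, add the 2-item Intentions to Cope scale to the pre-intervention questions in all three arms, alongside MHL, PHQ-2 and GAD-2. In Data analysis, name that score as a covariate in the Intentions to Cope model; without this second step the extra items gain no precision. In the same section, state that the intentions-to-cope covariate in the MHL model is this pre-intervention score, which gives it a source that the article does not currently describe.

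The cost is two more items in an interview of 60–90 minutes and a few words of protocol text. The downside is possible carry-over or priming from asking the items twice in one interview, as already accepted for the other three outcomes.
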